### Recruitment

Patients will be recruited in the Dutch specialized mental healthcare centers including GGZ inGeest (Amsterdam), Riagg Maastricht (Maastricht), Altrecht (Utrecht) and PsyQ (Haarlem, The Hague, Leiden). During the intake, patients will be checked for the in- and exclusion criteria. If patients are eligible they will be approached for participation in the study and receive a general information folder. Patients that cannot participate in the study treatment will receive treatment as usual (Fig. 2).

### Randomization and procedure

An independent research assistant will contact eligible patients one week after the intake procedure in order to give patients additional study information and to check if the patient is motivated to participate in the study. If no structured diagnostic interview has been completed yet during the intake procedure, the research assistant will plan a diagnostic interview (SCID-I/MINI). Subsequently, if the patient wants to participate and fulfills the inclusion criteria, the patient will be invited for an online baseline assessment and to sign informed consent. After the baseline assessment, the patient will be randomized in one of the four groups by using a computer script performing block randomization (e.g. one- versus twice weekly; CBT versus IPT). Randomization (patient level) will be pre-stratified according to severity (high severity = BDI score = > 30; low severity = BDI score < =29) and treatment site. A venipuncture by experienced nurses will be planned before the start of treatment. Besides the baseline assessment, the patient will be asked to complete monthly online assessments in the course of treatment (month 1–6) and follow-up assessments at month 9, 12 and 24. This means that the moments of assessment will be equal for each group. In addition, the therapist and patient will be asked to fulfill some questionnaires during the sessions. A second venipuncture will be planned after the end of treatment (month 6).

### Interventions

In the Netherlands, cognitive behavioral therapy (CBT) and interpersonal therapy (IPT) are the most frequently practiced evidence- based psychological interventions for depression. Both therapies are applied in weekly sessions in routine clinical settings. CBT for depression is based on the manual by Beck [1] and IPT is based on the manual by Klerman [2]. The interventions will be offered in the participating mental health centers. Participants in the experimental condition (twice-weekly sessions) will receive 16 sessions during the first 8 weeks of treatment, and 4 sessions during the last 8 weeks (up to 20 sessions during 16 weeks). Patients in the control condition (once-weekly sessions) will receive 16 sessions during the first 16 weeks and 4 sessions during the last 8 weeks (up to 20 sessions during 24 weeks). Treatment manuals are used for all interventions and both treatments will contain 12 to 20 sessions of 45 minutes, depending on the individual progress of the patients. Qualified therapists who received additional training from prof. [name] (CBT) and prof. [name] (IPT), experts in their respective modalities, will deliver the interventions. Therapists participate in only one of the therapy conditions (CT or IPT) and will consult each other on current cases in biweekly consultation meetings. The sessions will be videotaped.

### Instruments

An overview of all patient instruments per assessment is given in Table 1. An overview of therapist/observer ratings per assessment is given in Table 2.

**Table 1 Tab1:** Overview of patient instruments per time point (months)

Instruments		0	5	1	2	3	4	5	6	9	12	24
*Clinical outcomes*												
*Depression*												
Beck Depression Inventory II (BDI-II)^1^		x	x	x	x	x	x	x	x	x	x	x
Remission of Depression Questionnaire (RDQ)		x				x			x	x	x	x
*Quality of life*												
RAND-36		x	x			x			x	x	x	x
EQ-5D(5L)		x				x			x	x	x	x
Happiness question^a^		x	x	x	x	x	x	x	x	x	x	x
Mood question^a^	x	x	x	x	x	x	x	x	x	x	x	
Longitudinal Interval Follow-up Evaluation (LIFE)		x	x	x	x	x	x	x	x	x	x	x
*Cost-Effectiveness*												
Trimbos/iMTA questionnaire for Costs associated with Psychiatric Illness - update version 2012 (TiC-P)		x				x			x	x	x	x
*Process/Predictors*												
*-Therapy-specific-Therapist-patient relationship*												
Working Alliance Inventory (WAI)			x	x	x	x	x	x	x			
Motivation												
Autonomous and Controlled Motivation for Treatment		x	x	x	x	x	x	x	x			
Questionnaire (ACMTQ)												
*Compliance*												
Patient compliance ratings			x	x	x	x	x	x	x	x		
*Behavioral activation*												
Behavioral Activation for Depression Scale (BADS)		x	x	x	x	x	x	x	x			
*Automatic thoughts*												
Cognition Checklist (CCL)		x	x	x	x	x	x	x	x			
*Emotion regulation*												
Action Control Scale (ACS)		x							x			
*Childhood trauma*												
Childhood Trauma Questionnaire (CTQ)		x										
Treatment preferences		x										
Treatment expectations		x										
*Learning-*												
*CT Skills*												
Competencies of Cognitive Therapy Scale (CCTS)		x	x			x			x			
*IPT Skills*												
IPT Skill Inventory		x	x			x			x			
*Executive functioning*												
N-back task		x	x	x					x			
*Biological markers*		x							x			
Brain-Derived Neurotrophic Factor (BDNF)												
DNA methylation		x							x			
Oxytocin		x							x			
*Other measures*												
*Demographics*		x										
*Diagnostics*												
Structured Clinical Interview for DSM-IV		x										
Axis I Disorder (SCID-I)/MINI-Plus												
*Attribution of therapy effects*									x			
*Treatment evaluation*									x			

^a^Depressive symptoms, mood and happiness will be rated each session

**Table 2 Tab2:** Overview of therapist/observer instruments per time point (months)

Instruments	0	1	2	3	4	5	6	9	12	24
*Process/Predictors*										
*-Therapy-specific-*										
*Therapist-patient relationship*										
Working Alliance Inventory- Therapist (WAI-T)		x	x	x	x	x	x			
Working Alliance Inventory- Observer (WAI-O)		x	x	x	x	x	x			
*Compliance*										
Kept appointments										x
Replaced appointments										x
Therapist-rated compliance										x
*Therapist adherence*										
Collaborative Study Psychotherapy Rating Scale (CSPRS)										x
*-Learning-*										
*CT Skills*										
Competencies of Cognitive Therapy Scale-Therapist (CCTS-T)		x		x			x			
Performance of Cognitive Therapy Strategies (PCTS)										x
*Recall*										
Therapist-rated recall quality^a^		x	x	x	x	x	x			

Quality of recall will be assessed each session^a^

### Instruments: clinical outcome measures

#### Depression: Beck Depression Inventory II (BDI-II) [37–39, 42]

The BDI is a 21-item self-report instrument assessing depressive symptoms during the last two weeks. The items are rated from 0 to 3, with 3 for the most depressed mood. A score 0–13 indicates minimal depression, 14–19 mild depression, 20–28 moderate depression and 29–63 severe depression. The instrument can be answered in 5–10 minutes. Several studies have shown that the BDI-II also is a strong screening measure for depression [37, 42].

#### Quality of life: EQ-5D(5 L) [43, 44]

The EQ-5D consists of five health state questions (mood, symptoms of pain/discomfort, mobility, daily activities, self-care) on which respondents indicate their own health state on a scale from 0 (no problems) to 3 (severe problems) during the past week. In addition, patients will rate their overall health on a scale from 0 (worst possible health) to 100 (best possible health). The Dutch EQ-5D (5 L) tariff will be used to calculate Quality-Adjusted Life-Years (QALYs). The EQ-5D (5 L) was validated for the Dutch population [44].

#### Remission of depression: remission of depression questionnaire [45, 46]

The RDQ is a 41-item self-report questionnaire assessing symptoms of depression as well as other variables reported by patients as relevant to determining remission during the past week. The items are grouped into 7 domains: symptoms of depression (13 items), anxiety and irritability (5 items), features of positive mental health (11 items), coping ability (3 items), functioning (3 items), life satisfaction (3 items), and a general sense of wellbeing (3 items). Items are rated on a 3-point rating scale (not true (0) - always true (2)). The questionnaire has shown excellent psychometric qualities.

#### Quality of life: happiness question [47]

The question ‘If you were to consider your life in general, how happy or unhappy would you say you are, on the whole?’ can be rated on a 7-points scale (1 = completely unhappy – 7 = completely happy) and was used in 33 nation surveys, including the Netherlands. The happiness question (code = Code: O- HL/g/sq/v/7/a) was used in many studies. In addition, we will ask a happiness question focusing on the present day (‘How happy of unhappy would you say you are today?’).

#### Rand-36 [48]

The RAND-36 is an 36-item assessment of general health and disabilities and covers the following domains: psychical and social functioning, role restriction due to physical or emotional problems, mental health, energy, pain, and general health perception. The RAND-36 has shown to be a reliable, valid and sensitive measure [48].

#### Mood: mood question

Each session, patients will be asked to rate their current mood on a 0 (worst mood) -10 scale (best mood).

#### Longitudinal Interview Follow-up Evaluation (LIFE) [49]

The LIFE is a semi-structured interview that will be used by an independent rater to assess episodes and symptoms of depression retrospectively in the long-term follow-up phase. The LIFE has shown reliable and valid for characterizing the course of depression over the period of one year [50, 51].

### Instruments: cost-effectiveness

#### Trimbos/iMTA questionnaire for Costs associated with Psychiatric Illness (TiC-P) – updated version 2012 [52]

Societal costs in the past three months will be measured using the TiC-P. The TiC-P consists of two different parts: part one (16 items) compromises costs due to loss of production including absenteeism from paid and unpaid work, and presenteeism. Part two (4 items) focuses on use of (psychiatric) health care including primary and secondary care, complementary care and home care. For the valuation of health care utilization standard prices [53] will be used. Medication use will be valued using prices of the Royal Dutch Society for Pharmacy [54].

### Instruments: moderators and mechanisms of change

#### Therapist-patient relationship: working alliance inventory-short form [55–58]

The WAI intends to measure tasks (e.g. behaviors and cognitions that form the therapeutic process), bonds (e.g. positive personal attachments between patient and therapist) and goals (e.g. therapist and patient mutually endorsing and valuing the goals) as components of the therapeutic alliance. The questionnaire consists of 12 items rated on a 5-point Likert scale and will be filled out by both patient and therapist [59, 60]. All therapy sessions will be videotaped. Independent experts will rate the therapeutic alliance on a random selection of videotapes using the 12-item Observer version of the Working Alliance Inventory-Short (WAI-O-S). The instrument has shown to have adequate psychometric properties.

#### Motivation: autonomous and controlled motivation for treatment questionnaire [61]

The ACMTQ includes two six-item subscale in order to assess autonomous (identified; ‘I personally believe it is the most important aspect of becoming well’ and integrated; ‘Managing my depression allows me to participate in other important aspects of my life’) motivation and controlled (external; ‘Others would be upset if I didn’t” and introjective; ‘I would feel guilty if I didn’t do what my therapist said’) motivation.

The format of the questionnaire was adapted from the Treatment Self-Regulation Questionnaire (TRSQ; 61]. Patients are provided with a stem (‘I participate in therapy because’) and asked to rate twelve items on a 7-point rating scale (1 = strongly disagree - 7 = strongly agree). Internal consistency has been shown to be sufficient [62].

#### Compliance

Compliance will be operationalized as the amount of no-shows (not showing up without leaving a message), cancelled and replaced appointments. Patients will rate their effort in treatment before each session. Furthermore, the therapist will give a rating of patients compliance to the therapy at the end of treatment on a 7-point scale.

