
In this study, we hypothesize two pathways of change to be involved in the course of psychotherapy for depression (Fig. 1). First, we expect that a higher session frequency will enhance the quality of the relationship between patient and therapist. This relationship has been referred to as therapeutic alliance and involves the behaviors and processes within the session, patients’ and therapists’ objectives about therapy and the interpersonal attachment of mutual trust, confidence and acceptance. Previously, therapeutic alliance has been positively related to treatment outcome [24–26] while lower therapeutic alliance was associated with dropout [27]. Possibly, the relationship between patient and therapist will develop more rapidly when the contact is more intense. We expect that a better therapeutic alliance will lead to more patient motivation and compliance, as the therapist will have better opportunities to detect patient’s struggles in motivation and compliance. Subsequently, higher rates of motivation and compliance are expected to lead to better and faster treatment outcomes. The second pathway of change focuses on the process of learning. It is possible that a higher session frequency will increase patients’ learning processes resulting in better treatment outcomes. This seems congruent with previous studies that show that it is the survival of neurons born in the last five days that is important for learning [28]. Possibly, a higher frequency will increase the survival of neurons that are important for learning and as a consequence optimize learning processes. In this study, we will measure the degree the patient is able to recall the content of the previous session and the therapeutic-specific skills of the patient (e.g. cognitive therapy skills or interpersonal therapy skills). We expect that a higher session frequency will lead to better session recall that, as a consequence, will lead to the development of better therapy- specific skills. Better therapy-specific skills are expected to lead to better and faster treatment outcomes.

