#### Executive functioning: n-back task [73]

During the n-back task patients are asked if a letter on the screen matches a letter previously (1-back, 2- back, 3-back) presented for 500 ms with an interval of 2000 ms. First, the patient will be asked to run a test trial, where he will get elaborate feedback about the incorrect responses (‘The previous letter was X, this indicated you had to press the button’). Second, the patient will complete a 1-back trial (two minutes) and a 2-back trial (two parts of 2.5 minutes). Only when the patient performs well on the 2-back (e.g. 2/3 correct responses; a correct response means a correct press or a correct no-press), he will be forwarded to the 3-back part of the task that will also take five minutes (two parts of 2.5 minute). Amount of targets in each condition will be 33 %. Feedback will be given after a correct response (marked by a green V) or a miss (marked by a black X). Working memory load increases as the task progresses from 1- back to 3-back and is suggested to require executive processes. The task will take a maximum of 12.5 minutes. Accuracy of responses (hits – false alarms) and reaction times will be measured. To prevent fatigue of the online assessments the patient will be asked to do the n-back task at another day than the other questionnaires.

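### The attendance part of compliance is a raw count that depends on how many appointments are scheduled, and the example 3-back gate sits at the accuracy of never pressing

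*Protocol article*

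**What the plan says.** **Compliance.** The Compliance subsection of the protocol article says "Compliance will be operationalized as the amount of no-shows (not showing up without leaving a message), cancelled and replaced appointments". No denominator is given. Two further measures follow: "Patients will rate their effort in treatment before each session", and "the therapist will give a rating of patients compliance to the therapy at the end of treatment on a 7-point scale". Table 2 lists "Kept appointments" and replaced appointments among the compliance items, marked at a single assessment.

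The Mechanisms of change section places compliance on the first hypothesised pathway, where "higher rates of motivation and compliance are expected to lead to better and faster treatment outcomes". The same section requires change in a mediator to come before change in the outcome, so that reverse causation can be excluded.

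Under Interventions, "both treatments will contain 12 to 20 sessions of 45 minutes, depending on the individual progress of the patients". Both arms have a ceiling of 20 sessions. The twice-weekly arm has 16 in its first 8 weeks and 4 in the next 8. The once-weekly arm has 16 in its first 16 weeks and 4 in the next 8.

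**n-back.** The n-back subsection sends a patient on to the 3-back only after good performance on the 2-back. The example criterion is "2/3 correct responses; a correct response means a correct press or a correct no-press". It also says "Amount of targets in each condition will be 33" per cent. Performance is scored as hits minus false alarms, with reaction times.

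**The concern.** A count of missed appointments has a ceiling set by the number of appointments made. Here that number is partly an outcome, because treatment can end earlier in patients who progress well. A patient who improves quickly has fewer chances to miss a session, so a low count may reflect good progress rather than cause it. For a variable meant to explain outcome, that is the reverse path the protocol says it wants to exclude. The randomised factor also changes how many sessions have been scheduled by any date before week 24, so the frequency-to-compliance path can pick up an exposure artefact.

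The n-back issue is separate and smaller. A gate meant to select patients who cope with the 2-back should not be reachable by doing nothing. If correct omissions count and about two trials in three are non-targets, a patient who makes no response gets about two thirds of trials right.

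**Working it through.** **1. The plan's own figure.** From Interventions: twice-weekly 2 × 8 + 4 = 20, and once-weekly 1 × 16 + 4 = 20. The stated maximum of 20 reproduces in both arms.

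**2. Scheduled sessions by date**, assuming even spacing within each phase and no early ending:

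| Week | Twice-weekly | Once-weekly |
|---|---|---|
| 4 | 8 | 4 |
| 8 | 16 | 8 |
| 12 | 18 | 12 |
| 16 | 20 | 16 |
| 24 | 20 | 20 |

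**3. Expected misses.** Expected count = sessions × *p*, where *p* is the chance of missing any one appointment. The document gives no value, so *p* is assumed equal for all patients and ranged over 5%, 10% and 20%.

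| Comparison | *p* = 5% | *p* = 10% | *p* = 20% |
|---|---|---|---|
| Ends at 12 v 20 sessions | 0.6 v 1.0 | 1.2 v 2.0 | 2.4 v 4.0 |
| Week 8, twice- v once-weekly | 0.8 v 0.4 | 1.6 v 0.8 | 3.2 v 1.6 |
| End, 20 v 20 sessions | 1.0 v 1.0 | 2.0 v 2.0 | 4.0 v 4.0 |
| End, mean 16 v 20 (assumed) | 0.8 v 1.0 | 1.6 v 2.0 | 3.2 v 4.0 |

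The first row is the main one. The ratio is 20/12 = 1.67 at every *p*, with identical behaviour per appointment. The other rows show that the between-arm artefact changes sign with the date of counting. Twice-weekly looks less compliant at week 8, no different at 20 v 20, and more compliant at the end if that arm uses fewer sessions. The section on frequency of psychotherapy treats that last case as conceivable.

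**4. With a denominator.** Expected proportion = (sessions × *p*) / sessions = *p*, whatever the arm, date or treatment length.

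**5. The 3-back gate.** Share correct = *t* × hit rate + (1 − *t*) × (1 − false-alarm rate), where *t* is the target share. Never pressing means both rates are 0, so the share correct is 1 − *t*.

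- With *t* = 0.33: 0.67, just above 2/3 = 0.667.
- With *t* = 1/3: exactly 2/3, which passes if the rule is at least 2/3 and fails if it is more than 2/3.
- In whole trials over 5 minutes, assuming 120 or 150 trials: 40 or 50 targets give 80/120 or 100/150, both exactly 2/3. With 39 or 49 targets, 81/120 = 67.5% and 101/150 = 67.3% pass under either rule.
- On the protocol's own score, the same patient has hits minus false alarms = 0.

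**The case against.** The strongest reply on compliance is that attendance is only one of three measures. The effort rating and the 7-point therapist rating do not grow with the number of sessions, and Table 1 schedules patient compliance ratings repeatedly during treatment. Kept appointments are recorded, so a rate can be formed. The section on analysis of mechanisms of change does not say that a raw count enters the mediation model, and a fuller analysis plan might rescale it. All of that limits the point. What remains is that the article does state how this component is to be operationalised, and as stated it is a count.

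A reader might infer that the count always works against the twice-weekly arm. The documents do not support that: the direction depends on when the count is taken and how many sessions each arm uses, and no comparison of counts at week 8 is described.

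On the n-back, a reader might infer that the measure itself is invalid. It is not, because a patient who never presses scores 0, and the two-thirds rule is given only as an example for entry to the 3-back. A reader might also infer that the gate admits non-responders while excluding better performers, citing a patient with 80% hits and 40% false alarms. That patient gets 0.33 × 0.8 + 0.67 × 0.6 = 66.6% against 67.0% for never pressing, but at exactly one target in three both get 2/3, so this contrast is rounding. Patients also get feedback on errors in the test trial and a marker after each miss. The document gives no basis for judging how often anyone would persist in not pressing, or how far the 3-back sample would be affected.

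**Conclusion.** Both points hold in limited form and are minor.

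- **Attendance component.** The stated count depends on appointments scheduled, which depend in part on progress. At equal behaviour, a patient ending at 20 sessions expects 1.67 times the misses of one ending at 12 (1.0 to 4.0 against 0.6 to 2.4, for assumed miss rates of 5% to 20%). That builds reverse causation into one measure of a hypothesised mediator. The between-arm artefact can go either way and is nil if both arms use all 20 sessions. The absolute sizes rest on the assumed miss rate; the ratio rests only on that rate being equal across patients.
- **3-back gate.** The example threshold equals, to rounding, the accuracy of never pressing, so it does not screen out non-responders. This follows from the stated target share and scoring rule alone.

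The two compliance ratings, the n-back score, the BDI-II outcome and the sample size are unaffected.

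**What to change.** **Attendance.** Define this component as the proportion of scheduled appointments missed (or kept), with scheduled meaning kept plus missed and each replaced appointment counted once. For mediation, compute it in a fixed window that ends before the outcome it is to explain. Kept appointments are already collected, so the proportion needs only a scoring definition. The early window also needs dated attendance. Table 2 marks these items once, so the plan should confirm that dates can be recovered from the session records.

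**3-back.** Leave the running task unchanged, so that earlier and later patients remain comparable. At analysis, treat a patient's 3-back data as valid only if hits minus false alarms on the 2-back exceeds a positive value fixed beforehand. This uses data the task already records and costs one sentence in the analysis plan.
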